## Methods

The ULTRA-stroke program has been approved by the Medical Ethical Reviewing Committee of the VU University Medical Centre (protocol number 2008/296, Dutch Central Committee on Research Involving Human Subjects, CCMO, protocol number NL20456.029.08).

### Recruitment

Sixty patients, admitted to the Rehabilitation Centre Amsterdam (RCA), who meet the criteria within 6 months after stroke onset will be recruited. Both in- and outpatients will be enrolled.

The inclusion criteria are: a first-ever ischemic or hemorrhagic stroke in one of the hemispheres, as verified by CT and/or MRI scan; an upper limb deficit, however with minimal control of the paretic wrist and fingers (i.e., able to execute at least 10° of active wrist extension, at least 10° of thumb abduction/extension, and at least 10° extension in at least 2 additional digits); a score on the Action Research Arm Test (ARAT) of less than 53 points; between 18 and 80 years of age; written or oral informed consent; sufficient motivation to participate.

The exclusion criteria are: upper extremity orthopaedic limitations; not being able to communicate (i.e., < 4 points on the Utrecht Communication Observation, UCO [63]); a Mini Mental State Examination (MMSE) score of < 24 points [64]. Patients with a pacemaker or metallic implant will be recruited. However, they will not be subjected to MEG-recordings given the interference with the magnetic signal. There will be no restrictions with respect to gender, ethnicity, or socio-economic status.

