## Background

In the Netherlands, each year more than 32,000 patients sustain a stroke [1,2], and the incidence is expected to have increased by 30-45% by 2015 [3]. About 80% of stroke survivors suffer from an upper limb paresis immediately after stroke [4], hampering movement of the paretic arm and bimanual coordination [5].

Spontaneous recovery after stroke is limited, and knowledge about which mechanisms lead to spontaneous recovery is incomplete [6]. Restitution of non-infarcted penumbral tissue (i.e., reestablishment of metabolism in the tissues surrounding the infarcted area) [7] and resolution of diaschisis (i.e., relief of suppression of anatomically related brain areas) [8], together with recovery of neurotransmission in spared tissue near and remote from the infarct [7,8], are held mainly responsible for the nonlinear recovery pattern observed in the first weeks post-stroke [6].

In addition to these early post-stroke developments, functional recovery of the upper extremity is promoted by plastic changes in the functioning of the brain, which, in general, also occur in learning [9]. These experience-induced changes are brought about by a combination of neural repair and neuro-anatomic reorganization, and include greater excitability and recruitment of the neurons in both hemispheres, sprouting of dendrites, and strengthening of synaptic connections [7,10-16].

Although the aforementioned processes may suggest an optimistic view on post-stroke recovery, only one third of all stroke patients regain some dexterity within six months using conventional treatment programs [7]. This means that 60-70% of all stroke survivors will continue to experience major functional limitations of the upper extremity [17], which are associated with diminished health-related quality of life after stroke [7,18].

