### Design

The intake procedure will take place the week following informed consent. After the intake procedure, which will include the first assessment of outcome variables, patients will be stratified in those with some dexterity and those with minimal control of paretic wrist and finger extension. Patients with some dexterity are able to execute > 10° finger extension of each metacarpophalangeal and interphalangeal joint of all digits and > 20° wrist extension. Patients with minimal control are those who meet the criteria of inclusion (i.e., able to execute at least 10° of active wrist extension, at least 10° of thumb abduction/extension, and at least 10° extension in at least 2 additional digits), but not (yet) the criteria of some dexterity. After stratification, patients will be randomized in permuted blocks and allocated to one of the three intervention groups (i.e., modified BATRAC, modified CIMT, or DMCT). Concealed allocation is effectuated with an online, computerized randomization procedure according to the minimization method [65]. Other therapists and social workers will provide regular care depending on patient needs.

After the first assessment and randomization, an intervention period will take place for 6 consecutive weeks. The effects of the interventions are examined using a pretest-posttest design. The pretests (t0) are performed in the week prior to intervention and posttests (t1) are performed in the week after intervention. The degrees to which changes are sustained are examined using retention tests (t2), 6 weeks after completion of the intervention. Figure 1 shows the time schedule for effectuating the entire protocol. (Figure 1.)

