### Power analysis

The number of patients is based on a statistical power of 80% (preventing Type II error) with an alpha of 5% (preventing Type I error) for detecting a meaningful difference of 6 points on the ARAT as the primary measurement of outcome and expecting 15% drop-out. The statistical power for detecting 10% or 6 points difference between groups is based on the following power calculation:

(Z_1-α/2 _+ Z_1-β_)^2 ^= 10.43 (assuming an alpha of 0.017, corrected for multiple testing with 3 groups and a Beta of 0.80)

σ2 (expected variance of sample on ARAT) = 26

Δ2 (assumed difference in favour ARAT) = 36

r (expected ratio between intervention groups) = 1

Expected numbers needed per intervention group (N_per group_) = 15 (excluding expected drop out of less than 25%).

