### Outcome variables

The primary outcome variable will be the score on the Action Research Arm test (ARAT). Secondary outcome variables are the scores on the Motricity Index (MI) of the arm, Fugl-Meyer for the arm (FM-arm), Nine Hole Peg test (NHPT), Erasmus modification of the Nottingham Sensory Assessment (EmNSA), Motor Activity Log (MAL), and Stroke Impact Scale (SIS version 3.0). All assessments will be applied to all patients at t0, t1, and t2.

Non-parametric statistics for independent samples will be used [81]. A Kruskal-Wallis test will be used to examine whether improvements before and after intervention (from t0 to t1) were significantly different between the three intervention groups (i.e., BATRAC, CIMT, and DMCT). When a significant difference is found between the three groups, a *post-hoc *Mann-Whitney U test will be applied to reveal which groups (CIMT, BATRAC, or DMCT) differ significantly from each other. The same procedure will be used for observed changes after the 6 weeks retention period, i.e., from t1 to t2.

The ARAT is a valid, reliable, and responsive performance test [82] of the ability to perform gross movements and to grasp, move, and release objects differing in size, weight, and shape [83]. The minimal clinically important difference is set at about 10% of the scale's range, i.e., 6 points [84]; improvement by > 10 points is defined as return of dexterity [17].

The MI will be used to measure strength in upper extremities [85]. Higher scores represent greater strength in the upper limb. This instrument provides a reliable and valid assessment of the presence of paresis in stroke patients by testing 6 functions rated for each limb [64,85].

The FM arm score is a reliable and valid motor performance test consisting of 33 tasks performed by the affected upper limb [86,87]. The FM-arm test evaluates the ability to make movements outside the synergistic pattern. Performance on each task is rated as 0, 1, or 2, with higher rates representing better performance. The FM-arm measure will be used as the sum of 33 ratings (possible range 0 to 66 points).

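### Time since stroke may vary over the whole first 6 months, yet it is not used in the ARAT comparison or named as a balancing factor: a loss of precision, not a bias

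*Protocol article*

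**What the plan says.** All references are to the protocol article.

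- **Entry (Recruitment).** Rehabilitation-centre patients, both in- and outpatients, "who meet the criteria within 6 months after stroke onset will be recruited". No minimum time since onset is given.
- **Recovery curve (Background).** Several spontaneous processes "are held mainly responsible for the nonlinear recovery pattern observed in the first weeks post-stroke".
- **Balancing (Design).** After intake, "patients will be stratified in those with some dexterity and those with minimal control of paretic wrist and finger extension". Minimal control means meeting the inclusion criteria "but not (yet) the criteria of some dexterity". Permuted blocks are mentioned, and then: "Concealed allocation is effectuated with an online, computerized randomization procedure according to the minimization method". No factor other than dexterity is named.
- **Primary comparison (Outcome variables).** "A Kruskal-Wallis test will be used to examine whether improvements before and after intervention (from t0 to t1) were significantly different" between the three groups. If it is significant, a Mann-Whitney U "test will be applied to reveal which groups (CIMT, BATRAC, or DMCT) differ significantly from each other". The change from t1 to t2 is handled the same way. No covariate or stratum enters. The stratification is named as a grouping factor only for the stiffness measures (Peripheral stiffness).
- **Planning (Power analysis).** A difference of 6 points, a variance of 26, and 15 per group, "assuming an alpha of 0.017, corrected for multiple testing with 3 groups and a Beta of 0.80". Time since onset is not mentioned.

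**The concern.** The outcome analysed is a change score over about six weeks. If spontaneous recovery is steeper in the first weeks, two patients with the same baseline ARAT can have different expected gains in the same arm, simply because one entered early and the other late. The entry rule allows this mix, and the stated tests leave the resulting spread in the error.

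Two things are at stake. The first is precision and chance balance in a trial of 60 patients over three arms. The second is interpretation by dexterity stratum. The Background uses the stratum to address corticospinal integrity and expects modified CIMT to do better in patients with some dexterity. Membership is fixed on the day of assessment, so an early patient who is still improving and a late patient with the same extension angles share a stratum. That makes a difference between strata harder to read.

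**Working it through.** **Inputs from the article.** Difference 6 points, variance 26, alpha 0.017 two-sided, power 80% (I read the stated Beta of 0.80 as power), 15 per group before dropout, 60 patients, hence 20 per arm randomised. I show both 15 and 20 per arm because the Power analysis gives dropout as 15% in one place and under 25% in another.

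**Step 1: the plan's own figure.** n = 2σ²(z₁₋α/₂ + z₁₋β)²/Δ². The multiplier is (2.387 + 0.842)² = 10.42 (stated: 10.43). n = 2 × 26 × 10.43/36 = 15.07. The stated 15 reproduces (16 if rounded up), and 15/(1 − 0.25) = 20 per arm. There is no arithmetic error, but 15 per arm leaves no slack.

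**Step 2: baseline power.** Power = Φ(Δ/√(2σ²/n) − 2.387).
- n = 15: 6/√(52/15) = 6/1.862 = 3.22, power 80%.
- n = 20: 6/√(52/20) = 6/1.612 = 3.72, power 91%.

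This is the plan's normal approximation. It only approximates the rank tests actually named.

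**Step 3: assumed spread of spontaneous gain.** The article gives no figure. As an illustration, gain over 6 weeks for a patient entering at week t is g(t) = A[exp(−t/τ) − exp(−(t+6)/τ)], with A = 10, 20 or 30 points, τ = 4, 6 or 10 weeks, and t uniform from an earliest week (1, 2, 4 or 8) to week 26. Let s be the between-patient SD of g. If s² adds to 26:

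| Earliest entry | s (points) | Power, 15 per arm | Power, 20 per arm |
|---|---|---|---|
| week 1 | 1.0 to 4.2 | 78% to 54% | 90% to 68% |
| week 2 | 0.9 to 3.5 | 78% to 61% | 90% to 76% |
| week 4 | 0.7 to 2.5 | 79% to 69% | 90% to 83% |
| week 8 | 0.3 to 1.4 | 80% to 76% | 91% to 88% |

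Worst case in full: s = 4.24, s² = 17.98, total variance 43.98. 6/√(2 × 43.98/15) = 6/2.42 = 2.48; 2.48 − 2.39 = 0.09; power 54%.

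A variant with 7 weeks between tests, A = 20 or 30, τ = 4 to 8 and entry from week 2 or 4 gives s = 1.5 to 3.8, inside the same range.

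**Step 4: chance imbalance.** The SD of the arm difference due to onset times alone is √(2s²/n). At s = 4.24 this is √(2 × 17.98/15) = 1.55 points with 15 per arm and √(2 × 17.98/20) = 1.34 with 20, against a target of 6. At s = 2 it is 0.73 and 0.63. This is the same variance as in Step 3 seen from another side, not a second loss.

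**Step 5: if 26 already contains s².** Nothing is lost against plan. Full adjustment would leave a residual variance of 26 − s²: 22 (s = 2), 17 (s = 3) or 10 (s = 4). The n per arm for 80% power would fall from 16 to 13, 10 or 6. These are best cases, because a banded or log covariate captures only part of s².

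**The case against.** The strongest reply is that randomisation with three concurrent arms already deals with spontaneous recovery: it cancels in expectation. That stands. A reader might infer that the contrast is biased; the documents do not support this. Chance imbalance is ordinary sampling error, and with variance 26 and 20 per arm the SE of a difference is already 1.6 points.

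Other objections that stand:
- **The size is assumed.** Patients come from a rehabilitation centre, must already have some wrist and finger extension, and pass through an intake week, so very early entry may be rare. Inclusion runs up to an ARAT of 52, so some patients have little room to gain, while the model gives everyone the same scope.
- **The variance of 26 may already include this spread.** The article does not say.
- **Further minimisation factors may exist.** The article is condensed, and its silence does not show that time since onset is left out of the allocation.
- **No ARAT test by stratum is specified.** The stratum point therefore concerns how a stated hypothesis will be read, not a defined analysis.

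Two further inferences are tempting but fail. The Background does not say that dexterity is settled by six months or that late entrants gain almost nothing. It says that about one third regain some dexterity in that time on conventional treatment. Nor do late entrants breach the trial's window: six months limits recruitment, and nothing requires training or follow-up to end by then.

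These objections do not reach the stated primary analysis. The article names the tests, and as named they take neither a covariate nor a stratum.

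**Conclusion.** The point holds as one of precision. The plan admits patients over a period in which, by its own account, recovery is nonlinear early on, and then compares ARAT change without using time since onset or even the dexterity stratum.

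The loss ranges from negligible to material, and the documents cannot place it within that range. If few patients enter before about week 8, power with 15 per arm stays at 76% or above. If patients enter from the first weeks with a large scope for recovery, and the variance comes on top of 26, it could fall to about 54% (68% with 20 per arm). A reader might conclude that the trial is underpowered. That does not follow, because it depends on the assumed recovery curve, the uniform entry and whether 26 already covers the spread. In either case, adjusting for a prognostic value already in hand can be expected to gain precision. No change to the entry limit follows from this.

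**What to change.** 1. **Primary test.** Replace the unadjusted Kruskal-Wallis and Mann-Whitney tests of ARAT change with a rank ANCOVA using weeks since onset (log, or two to three bands) and the dexterity stratum. A stratified rank test of the van Elteren type is an alternative. With two strata and three bands it has six cells averaging 60/6 = 10 patients over three arms, so two bands (60/4 = 15 per cell) or the rank ANCOVA is safer. Treat the t1 to t2 comparison in the same way.
2. **Allocation.** If the full protocol does not already include it, add banded weeks since onset to the online minimisation. Do not add it as further permuted-block strata, where cells of about ten patients could leave blocks incomplete.
3. **Reporting.** Take weeks since onset into account when presenting results by dexterity stratum.

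The cost is one more field in the randomisation system and a slightly more complex allocation. The primary test is replaced, not merely extended, since the named tests cannot take a covariate. No new data are needed, because the onset date must be known to check eligibility.

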### Design

The intake procedure will take place the week following informed consent. After the intake procedure, which will include the first assessment of outcome variables, patients will be stratified in those with some dexterity and those with minimal control of paretic wrist and finger extension. Patients with some dexterity are able to execute > 10° finger extension of each metacarpophalangeal and interphalangeal joint of all digits and > 20° wrist extension. Patients with minimal control are those who meet the criteria of inclusion (i.e., able to execute at least 10° of active wrist extension, at least 10° of thumb abduction/extension, and at least 10° extension in at least 2 additional digits), but not (yet) the criteria of some dexterity. After stratification, patients will be randomized in permuted blocks and allocated to one of the three intervention groups (i.e., modified BATRAC, modified CIMT, or DMCT). Concealed allocation is effectuated with an online, computerized randomization procedure according to the minimization method [65]. Other therapists and social workers will provide regular care depending on patient needs.

After the first assessment and randomization, an intervention period will take place for 6 consecutive weeks. The effects of the interventions are examined using a pretest-posttest design. The pretests (t0) are performed in the week prior to intervention and posttests (t1) are performed in the week after intervention. The degrees to which changes are sustained are examined using retention tests (t2), 6 weeks after completion of the intervention. Figure 1 shows the time schedule for effectuating the entire protocol. (Figure 1.)

**Figure 1 F1:**
[figure not shown]
**Timepath**. Participant flow through the trial.

### Interventions

The interventions will be applied by physiotherapists and/or occupational therapists working at the RCA. If possible, interventions will be applied in groups with no more than 3 patients per group in a treatment session.

### Modified BATRAC

The modified BATRAC group receives 60-minute sessions, 3 days a week for 6 consecutive weeks. Treatment will be applied in 3-minute movement periods interspersed with 5-minute rest periods (i.e., effectively 21 minutes of active movements). During the rest periods and before the first exercise, patients will receive visual and oral feedback on the previous exercise (when applicable) and instructions for the following exercise. The movements during the exercises are paced by an auditory metronome. The tempo of the auditory cues depends on the severity of the upper limb deficit and is selected individually. Over the course of training the tempo is adjusted in response to improvement in task performance.

#### Apparatus

During therapy, custom-made modified BATRAC-apparatuses (developed at the Faculty of Human Movement Sciences of VU University Amsterdam) will be used (see Figure 2A). The apparatus is mounted on a chair with arm rests. At the distal end of each arm rest, a manipulandum with a handgrip is fitted which allows motion in the horizontal plane. In front of the patient, between the arm rests, a removable table top is placed. The patient is seated on the prepared chair, with the ankles in neutral dorsiflexion and knees and hips placed at 90°. The patient's hands are vertically fixated to the handgrips and the lower arms are fixated to the arm rests with Velcro straps. These fixations, together with an adjustable stop at the proximal end of the arm rests, allow flexion and extension movements of the wrist only. The distance of the handgrip on the manipulanda is adjustable to make sure the rotation axis of the wrist is aligned with that of the manipulandum.

**Figure 2 F2:**
[figure not shown]
**Modified BATRAC exercise apparatus**. A: the modified BATRAC exercise apparatus. The apparatus allows movements in the horizontal plane only. The rotation axis of the wrist is aligned with that of the manipulandum B: a feedback screenshot. On the left, left-hand position by right-hand position (white) and ideal line of movement are depicted. On the top-right the amplitudes for flexion and extension for both hands separately are given. On the bottom right the relative phase and its variability for flexion and extension are presented.

Below the manipulanda, potentiometers (FCP40A, tolerance ± 0.1%, Sakae Tsushin Kogyo Co., Ltd., Nakahara-ku, Kawasaki-city, Japan) are attached that measure the movements (i.e., wrist rotation) during exercise. A computer connected to the potentiometers registers these movements and provides feedback. The computer is also used to start each exercise, i.e., exercise type (see below) and pacing frequency are set via the computer. The auditory cues (duration 50 ms, pitch 440 Hz) are generated by the computer and presented through headphones. (Figure 2.)

#### Goals

BATRAC has been motivated from research on the interlimb interactions governing bimanual coordination. Bimanual coordination is characterized by both spatial and temporal interactions [43,66]. The interactions become apparent when two limbs are instructed to move at unequal frequencies [49] or amplitudes [67] or by the fact that for isofrequency coordination (i.e., the limbs move at identical frequencies) only two coordination patterns can be performed stably without practise: in-phase (i.e., the limbs oscillate symmetrically) and antiphase (i.e., the limbs oscillate in an alternating fashion) [68].

The primary goal of modified BATRAC is to optimize the coordination between both hands. In the context of BATRAC, this means that temporal coupling between rhythmic hand movements (i.e., flexion and extension movements) in the two intrinsically stable coordination patterns (i.e., in-phase and antiphase) will be utilized. To achieve optimization of coordination, a large number of repetitive movements will be performed at a specified frequency during the exercises outlined below.

Although these exercises may seem unrelated to the functional goal of regaining voluntary control over hand function in daily situations, their motivation resides in the conjecture that hand function improves when the least-affected hemisphere facilitates controlling the movements of the paretic arm. Following this principle, optimization of coordination between both upper extremities is beneficial for regaining functional ability and functional use [19,20].

The second goal of modified BATRAC is to increase the range of motion of the wrist, with a strong emphasis on active wrist and finger extension. Loss of hand function is problematic because it is crucial to manual exploration and manipulation of the environment, and thus a major source of disability in stroke. The increase in force control associated with the generation of larger movement amplitudes, especially towards wrist and finger extension, will contribute to fine motor control, as this is required in manipulating and releasing grasped objects.

